#### **4.3 Screening Failures:**

Patients who signed the ICF but were found not eligible for the study prior to receiving study drug are defined as screening failures. For these patients, only limited information will be collected in the case report form (CRF):

- Informed consent
- Demographics

- Inclusion/exclusion criteria
- SAE and/or death occurring during the screening period.

## 5 Treatment

### 5.1 Dosage and Treatment cycle of Study drug

#### 5.1.1 Phase Ib Study

**Objective:** To determine the MTD and DLT/RP2D of Chidamide.

**Methods:** Traditional “3+3” design.

**Sample Size:** 9-18 patients

| Design | Method Description                                                                                                                                                                                                                                                                                                                                                                                                                                                                                                                                                                                          |
|--------|-------------------------------------------------------------------------------------------------------------------------------------------------------------------------------------------------------------------------------------------------------------------------------------------------------------------------------------------------------------------------------------------------------------------------------------------------------------------------------------------------------------------------------------------------------------------------------------------------------------|
| “3+3”  | 
 
Starting from the initial dose, there are 3 subjects at each dose level;
 
Proceed to the next level of dose level test according to the established dose escalation plan, if DLT does not occur.
 
If 1 case of DLT occurs, 3 more subjects are added to the dose level. Proceed to the next dose level test once no new DLT appears.
 
If more than 2 cases of DLT occur, the forward dose level of this dose level is defined as MTD.
 
MTD is defined as when at a dose level less than 2 cases of DLT out of 6 subjects.
 
 |

RP2D is determined according to MTD and DLT.

- Initial dose of chidamide: 3 dose groups (20mg, 25mg, 30mg) with 3 to 6 subjects in each group. The starting dose is 20 mg per dose twice a week for continuous oral administration. If DLT does not occur, follow the established dose escalation plan to proceed to the next dose level test. If there is 1 case of DLT, add 3 more subjects to this dose level. When no new DLT appears, proceed to the next dose level. If there are more than 2 cases of DLT, the forward dose level of this dose level is defined as MTD.
- Sintilimab dose: 200mg/time (fixed dose)

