### 3.3 Treatment Period

In phase Ib, patients received oral escalating doses of chidamide (20, 25, 30 mg) twice a week continuous and fixed doses of 200mg sintilimab intravenously over a period of 30–60 min, once every 21 days. If DLTs does not occur, the established dose escalation plan could be proceeded to the next level. If one case of DLT occurs, 3 more subjects should be added to this dose level until there is no new DLT report. If there are more than 2 cases of DLT, the forward dose level of this dose level is defined as MTD. The dose level of Sintilimab is 200 mg (fixed dose) each time and repeated every three weeks. Patients that achieved CR and PR could receive for up to one-year treatment. Patients defined with SD and PD should withdraw from the study.

The phase II study is proceeded according to the RP2D of Chidamide. Patients that achieved CR and PR could receive for up to 12 months treatment, otherwise until disease progression, death, intolerable toxicity, completion of the scheduled treatment cycle, or the investigators' decision to withdraw (whichever occurs first).

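### The phase Ib 3+3 rules state no action for exactly two DLTs, so on some paths the MTD and the phase II dose are indeterminate

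*Protocol*

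**What the plan says.** The table in Protocol Section 5.1.1 sets out the escalation in five steps, with three subjects per level at the start:

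- No DLT: "Proceed to the next level of dose level test according to the established dose escalation plan, if DLT does not occur".
- One DLT: "If 1 case of DLT occurs, 3 more subjects are added to the dose level", followed by "Proceed to the next dose level test once no new DLT appears".
- Three or more DLTs: "If more than 2 cases of DLT occur, the forward dose level of this dose level is defined as MTD". The level called forward is read here as the one below.
- Definition: "MTD is defined as when at a dose level less than 2 cases of DLT out of 6 subjects".

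The bullet under the table repeats the threshold: "If there are more than 2 cases of DLT, the forward dose level of this dose level is defined as MTD". Section 3.3 uses the same threshold again. On expansion after one DLT, Section 3.3 says "3 more subjects should be added to this dose level until there is no new DLT report".

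The phase II dose depends on the result. Section 5.1.1 states "RP2D is determined according to MTD and DLT", Section 10.1 takes the phase Ib MTD as the recommended phase II dose, and Section 3.1 starts phase II only once MTD, DLT and RP2D are determined. Phase Ib is sized at 9 to 18 patients: three dose levels with three to six patients each.

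**The concern.** The rule that assigns the MTD starts at three DLTs, while the definition of the MTD ends at one DLT in six. A level with exactly two DLTs falls between them. It does not trigger the assignment rule and it cannot itself be the MTD. The gap is not a single stray phrase: the threshold appears in the table, in the bullet and in Section 3.3, and no other passage closes it.

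Two DLTs is one of the outcomes that a 3+3 scheme most needs to resolve. If it occurs, sites and sponsor must decide outside the protocol which level is the MTD, and that choice fixes the dose for all 28 phase II patients.

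**Working it through.** **Sample size as stated.** 3 levels × 3 = 9 and 3 levels × 6 = 18, which reproduces the 9–18 range.

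**Decision table from Section 5.1.1.**

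| DLTs at a level | Stated action |
|---|---|
| 0 of 3 | escalate |
| 1 of 3 | add three patients |
| 1 of 6 | escalate |
| 2 of 3 | none |
| 2 of 6 | none |
| 3 of 3, 3 of 6, 4 of 6 | MTD assigned to the forward level |

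**How often a level ends with exactly two DLTs.** The protocol gives no DLT rate for the combination, so the rate d is an assumption and a range is shown. With independent patients,

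P(exactly 2) = P(2 of 3) + P(1 of 3)², where P(2 of 3) = 3d²(1−d) and P(1 of 3) = 3d(1−d)².

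| d | P(2 of 3) | P(1 of 3)² | Sum |
|---|---|---|---|
| 5% | 0.007 | 0.018 | 2.5% |
| 10% | 0.027 | 0.059 | 9% |
| 20% | 0.096 | 0.147 | 24% |
| 25% | 0.141 | 0.178 | 32% |
| 33% | 0.219 | 0.198 | 42% |
| 40% | 0.288 | 0.187 | 47% |

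The written rule for three or more DLTs applies with probability 0.8%, 4.8%, 12.2% and 21.6% at d = 10%, 20%, 30% and 40%. Of all outcomes that do not permit escalation, exactly two DLTs therefore makes up 92%, 84%, 76% and 69%.

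**When the MTD is left open.**

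- After 2 of 3, nothing says whether the cohort closes or is filled to six, nor which level is then the MTD.
- After 2 of 6, the level fails the definition. The definition identifies another level only if the one below has six patients with fewer than two DLTs. A level that was passed with 0 of 3 has only three patients, and the starting level has none below it.
- If the level below had 1 of 6, the definition points to it.

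**Over the whole escalation.** Take assumed rates of 10/20/30% at the three levels and no escalation after two DLTs. The probabilities of passing levels 1 and 2 are 0.906 and 0.709.

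- Halting at exactly two: 0.086 + 0.906 × 0.2435 + 0.906 × 0.709 × 0.3835 = 0.55.
- Halting there with 0 of 3 at the level below, or with no level below: 0.086 + 0.729 × 0.2435 + 0.906 × 0.512 × 0.3835 = 0.44, where 0.729 and 0.512 are P(0 of 3) at levels 1 and 2.

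The corresponding pairs are 32% and 27% for rates of 5/10/20%, and 68% and 56% for 20/30/40%. The second figure in each pair treats any halt above a 1-of-6 level as resolved, including a halt at 2 of 3.

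**Secondary check on the range.** With no DLT anywhere, 3 + 3 + 3 = 9 patients are treated, only three of them at the top level. No rule expands a level without DLTs, so that path does not provide the six subjects in the definition. If all three levels are climbed and six are required at the MTD, the path needs at least 3 + 3 + 6 = 12.

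**The case against.** The intent can probably be recovered. Sections 3.1 and 5.1.1 call the scheme a standard or traditional 3+3, and a threshold of two or more would be the exact complement of the definition's fewer than two, so a translation slip is plausible. That explains the text but does not repair it: the threshold is stated three times and never in the other form.

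Four stronger readings are tempting, and the documents do not support them.

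- A reader might infer that escalation from a level with two DLTs is allowed. It is not. Escalation is permitted only after no DLT, or after one DLT with no new one among three more patients. What is missing is the assignment of the MTD, not a bar on escalating.
- A reader might infer that the rules ignore everything below three DLTs. They act on 0 and 1 as well; the gap is exactly two.
- A reader might take Section 3.3 to allow repeated additions of three. The wording differs from Section 5.1.1, but the limit of three to six subjects per group in Sections 5.1.1 and 10.1 caps it.
- A reader might conclude that RP2D is undefined whenever two DLTs occur. It is not when the level below had 1 of 6.

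Low DLT rates also belong in the range. Section 1.1 reports that, in the single-agent chidamide phase I study, DLTs occurred only in the 50 mg three-times-weekly cohort. At 5% the gap is reached at a given level with probability of only 2.5%. The combination could be more toxic, and the protocol does not say.

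On the sample size, Section 10.1 says approximately, an early stop would use fewer than nine patients, and with no DLT at any level it is arguable that no MTD was reached. The point is therefore secondary, although some tension remains because Section 10.1 equates the MTD with the phase II dose.

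**Conclusion.** The inconsistency is real and should be corrected. The assignment rule and the MTD definition leave exactly two DLTs without a stated action, and no rule says which level then becomes the MTD. The MTD and RP2D are indeterminate when the level below had only three patients treated or does not exist, and after 2 of 3 even the handling of the cohort is unstated. Because the phase II dose is taken from this result, this is a faulty decision threshold and not a detail that can be left to a later document.

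The per-level probability of meeting the gap runs from about 2.5% at a DLT rate of 5% to about 47% at 40%. These figures rest on assumed DLT rates and independent patients. The mismatch between the 9-patient path and the six-subject definition is a lesser point and holds only if six patients are in fact required at the MTD.

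**What to change.** Reconcile the steps and bullet of Section 5.1.1 with Section 3.3 so that every DLT count out of three and out of six, including exactly two, leads to one action that agrees with the stated MTD definition. State the expansion after one DLT in the same words in both sections. Then make the 9–18 range in Sections 5.1.1 and 10.1 consistent with the reconciled definition, including what happens when no DLT is seen at any level. Which rule and which dose apply is for the sponsor to decide; none is proposed here.

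The cost is an amendment of wording. If six patients are required at the top level on the path without DLTs, that path grows from 9 to 12, three more patients and within the stated 18.

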of PD-L1, and potential mechanism is via EBV triggering of latent membrane protein 1 (LMP1), which then upregulates PD-L1 expression through activation of the mitogen-activated protein kinases pathway/nuclear factor kappa B pathway. PD-1/PD-L1 show promising monotherapy efficacy and well tolerance in ENKTL failing to asparaginase-based treatment in current early-phase trials and retrospective studies. The ORR was about 38%-68% and CR rate was about 24%-36%. However, the median progression-free survival (PFS) and duration of response (DOR) are relatively short. Combining other therapies might be an approach to improve the efficacy.

Histone deacetylase inhibitors (HDACi) have shown promising effect in peripheral T cell lymphoma (PTCL). Chidamide an oral subtype-selective histone deacetylase inhibitor (HDACi) has been approved by National Medical Products Administration (NMPA) for the treatment of refractory or relapsed PTCL. In phase I study of chidamide monotherapy in patients with advanced solid tumors and lymphomas. Patients received oral doses of 5, 10, 17.5, 25, 32.5, or 50 mg chidamide either twice (BIW) or three times (TIW) per week for 4 consecutive weeks every 6 weeks. Two incidences of grade 3 diarrhea, nausea and vomiting of first-cycle dose-limiting toxicity (DLT) were observed in the first two patients enrolled in the 50 mg TIW cohort. Thus, gastrointestinal side effects were determined to be DLTs in the 50 mg TIW cohort. No DLTs were observed in other cohorts for both BIW and TIW regimens. In an exploratory phase II trial, 19 patients with relapsed or refractory PTCL were randomized to receive 30 or 50 mg twice per week for 2 weeks, followed by 1 week of rest. The ORR was 11.1% for the 30 mg and 40.0% for the 50 mg. One patient in the 50 mg arm experienced drug-related grade 4 thrombocytopenia. Based on the overall results from the phase I and exploratory phase II trials, patients in the pivotal phase II study were orally administered with chidamide of 30mg. However, efficacy

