### **3. Study Design**

#### **3.1 Overall Study design**

This is a phase Ib/II study including dose exploration, followed by the multi-center, open-label extended study.

The dose exploration of the Phase Ib study, a standard “3+3” design was utilized to identify the maximum tolerated dose (MTD), dose limited toxicities (DLTs) and recommended Phase II dosage (RP2D) of chidamide in combination with sintilimab. Once the MTD, DLT and RP2D of Chidamide is determined, the Phase II study shall begin.

The phase II study is proceeded according to the RP2D of chidamide. Patients that achieved CR and PR could receive for up to one-year treatment, otherwise until disease progression, death, intolerable toxicity, completion of the scheduled treatment cycle, or the investigators' decision to withdraw (whichever occurs first). After 12 months, patients still with CR or PR were allowed to choose to continue or end of treatment or accepted autologous hematopoietic stem cell transplantation (ASCT) as consolidation (Stem cell mobilization, collection, reinfusion, conditioning regimen prior to autologous hematopoietic stem cell transplantation followed the medical routine at each study site). If patients choose to continue sintilimab plus chidamide, doses of chidamide reduce to 20mg twice a week and fixed doses of 200mg sintilimab intravenously every 30 days. Dose interruptions were allowed for treatment-related adverse events until these events resolved to grade 0–1 or to baseline level. Treatment was permanently discontinued for patients who had interruptions of more than 4 weeks. Patients will be visited for end of treatment within 4 weeks after the end of the study. For those whose condition is stable or improved after treatment, progression-free survival (PFS) follow-up will be carried out 8 weeks after the last administration of the study drug, and

continued every 12 weeks thereafter until disease progression, death, withdrawal of informed consent (ICF), receiving other novel treatments, or termination of the entire study (whichever occurs first). At the same time, patients who have developed PD will be followed up for overall survival (OS) every 12 weeks until death, withdrawal of ICF, or the termination of the entire study (whichever occurs first). The survival follow-up is conducted every 8 weeks for patients with disease progression.

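### The phase Ib 3+3 rule steps down to the lower chidamide dose only after more than 2 DLTs, so exactly 2 DLTs usually leaves the MTD without a rule

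*Protocol*

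**What the plan says.** Section 3.1 calls the phase Ib design a standard 3+3, and section 5.1.1 calls it traditional. The rules in the section 5.1.1 table are, in substance:

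- Step 1: three subjects at each level to begin with.
- Step 2: escalate if no DLT occurs.
- Step 3: after 1 DLT add three subjects, and escalate if no new DLT appears.
- Step 4: "If more than 2 cases of DLT occur, the forward dose level of this dose level is defined as MTD".
- Step 5: "MTD is defined as when at a dose level less than 2 cases of DLT out of 6 subjects".

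Below the table stands "RP2D is determined according to MTD and DLT". The bullet that follows sets "3 dose groups (20mg, 25mg, 30mg) with 3 to 6 subjects in each group" and repeats the threshold: "If there are more than 2 cases of DLT, the forward dose level of this dose level is defined as MTD". Section 3.3 states the same threshold a third time and words the expansion differently: "3 more subjects should be added to this dose level until there is no new DLT report".

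Section 7.1.1 lists the MTD, DLT and RP2D of chidamide among the primary outcome measures. Section 3.1 ties phase II to them: "Once the MTD, DLT and RP2D of Chidamide is determined, the Phase II study shall begin". Section 10.1 takes the phase Ib MTD as the recommended phase II dose.

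**The concern.** Steps 4 and 5 use boundaries that do not meet. Step 4 acts from 3 DLTs upwards, while step 5 accepts at most 1 DLT in 6. The count of exactly 2 falls between them, and it is the most common way for a 3+3 level to fail.

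The two steps also conflict where step 4 does apply. Step 4 would declare as MTD a lower level that was passed at 0/3, although step 5 requires 6 subjects and no sentence expands that level.

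At stake is the traceability of a primary outcome that fixes the phase II dose. After exactly 2 DLTs the lower dose would be chosen by judgement, possibly on 3 subjects, and not by the stated rule.

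**Working it through.** **The plan's own figure.** The phase Ib size of 9 to 18 reproduces: 3 levels × 3 = 9 and 3 levels × 6 = 18.

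**Every ending of one level against the written steps** (p is the true DLT probability at that level; the word forward is read as the preceding level):

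| Ending | Probability | Written rule |
|---|---|---|
| 0/3 | (1−p)³ | Step 2: escalate |
| 1/3 then 0/3 | 3p(1−p)⁵ | Step 3: escalate |
| 2/3 | 3p²(1−p) | None names the lower level |
| 1/3 then 1/3 | 9p²(1−p)⁴ | None names the lower level |
| More than 2 | p³ + 3p(1−p)²[3p²(1−p) + p³] | Step 4: lower level is MTD |

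At exactly 2 DLTs, steps 2 and 3 do not allow escalation, step 4 is not triggered, and step 5 excludes the level because 2 is not less than 2. There are then three cases for the level below:

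- It was passed at 1/6. Step 5 makes it the MTD unaided, so this case is covered.
- It was passed at 0/3. It has 3 subjects, and nothing names or expands it.
- The event is at 20 mg. No lower level exists, and no outcome is stated.

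**Inputs.** The protocol gives no DLT rate for the combination, so all rates are assumptions.

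| p | 0/3 | 1/6 | Exactly 2 | More than 2 |
|---|---|---|---|---|
| 5% | 0.8574 | 0.1161 | 0.0255 | 0.0011 |
| 10% | 0.7290 | 0.1771 | 0.0860 | 0.0078 |
| 20% | 0.5120 | 0.1966 | 0.2435 | 0.0479 |
| 30% | 0.3430 | 0.1513 | 0.3835 | 0.1223 |

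**Over the three levels.** The chance of escalating from a level is the sum of the 0/3 and 1/6 columns: 0.9734 at 5% and 0.9061 at 10%. Exactly 2 DLTs with the level below at 0/3 has probability

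P(0/3 at 20 mg) × P(2 at 25 mg) + P(escalate from 20 mg) × P(0/3 at 25 mg) × P(2 at 30 mg).

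- 5/5/5%: 0.8574 × 0.0255 + 0.9734 × 0.8574 × 0.0255 = 0.043
- 5/10/20%: 0.8574 × 0.0860 + 0.9734 × 0.7290 × 0.2435 = 0.247
- 10/20/30%: 0.7290 × 0.2435 + 0.9061 × 0.5120 × 0.3835 = 0.355

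| Ending of the trial | 5/5/5% | 5/10/20% | 10/20/30% |
|---|---|---|---|
| Exactly 2, level below at 0/3 | 4.3% | 24.7% | 35.5% |
| Exactly 2 at 20 mg | 2.5% | 2.5% | 8.6% |
| **Uncovered, sum of the two** | **6.9%** | **27.2%** | **44.1%** |
| Exactly 2, level below at 1/6 (step 5 applies) | 0.6% | 5.2% | 11.1% |
| More than 2 (step 4 applies) | 0.3% | 5.1% | 13.0% |
| 30 mg passed at 0/3 | 81.2% | 45.2% | 22.0% |
| 30 mg passed at 1/6 | 11.0% | 17.3% | 9.7% |

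Each column sums to 100% apart from rounding. The bold sums are taken before rounding.

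**The case against.** The strongest reply is that the intent is plain. The design is labelled a standard or traditional 3+3, and the complement of step 5's limit is 2 or more. Once a level can neither be escalated from nor be the MTD, stopping and going down is the only sensible course. That makes this a wording slip, and the protocol lets the RP2D rest on the MTD and the DLTs together, so a tolerated lower dose remains available. As a reading of intent, this stands. But the label does not override a threshold written three times, and it does not say whether a lower level left at 0/3 must be expanded.

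It can also be said that DLTs may be rare. Section 1.1 reports monotherapy DLTs only at 50 mg three times weekly: "No DLTs were observed in other cohorts for both BIW and TIW regimens". Those cohorts included 32.5 mg and 50 mg, and section 5.7 describes 30 mg twice weekly as the pivotal-study dose. This stands too, and favours the low end of the range, although toxicity of the combination is not known from the document.

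Three stronger readings are tempting and should not be drawn:

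- A reader might infer that patients could be escalated after 2 DLTs. Section 5.1.1 allows escalation only at 0/3 or 1/6, and the cap of 6 per group limits exposure.
- A reader might count every ending with exactly 2 DLTs (7%, 32% and 55%). That includes endings in which the lower level stands at 1/6 and step 5 already names it.
- A reader might add the endings with 30 mg at 0/3. Groups of 3 to 6 are planned, so a group of 3 was foreseen. How to report it is a separate choice and adds no weight here.

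**Conclusion.** The step-down threshold is wrong as written and should be corrected. It contradicts step 5, leaves most endings with exactly 2 DLTs without a rule, and would name a 0/3 level as MTD against the 6 subjects that step 5 requires. The uncovered share is 6.9%, 27.2% or 44.1% of trials under the three assumed rate sets. It rests on independent DLTs at a constant rate per level, on stopping at exactly 2, and on the cap of 6 per group. Reading section 3.3 as allowing another expansion after 2/6 would break that cap and still not name the lower level.

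The consequence is limited to how the MTD, and with it the phase II dose, is established. The documents do not support a claim of unsafe escalation or of an error in the planned 9 to 18 patients.

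**What to change.** In section 3.3, the section 5.1.1 table and the bullet below it:

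1. Set the threshold at 2 or more DLTs (of 3 or of 6).
2. Replace the forward dose level by the next lower dose level.
3. Expand that lower level to 6 if only 3 were treated. Declare it the MTD if fewer than 2 of 6 have a DLT; otherwise step down again by the same rule.
4. State that 2 or more DLTs at 20 mg means no MTD in the tested range.
5. In section 3.3, replace the open-ended addition of subjects by a single expansion to 6.

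The cost is wording in three places, plus up to 3 extra patients at each lower level that is expanded. With at most 6 at each of three levels, the maximum stays at 18.

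A separate, optional clarification is what follows 0/3 at 30 mg: expand to 6, or report that the MTD was not reached. Expanding would raise a DLT-free run from 3 + 3 + 3 = 9 to 3 + 3 + 6 = 12 patients.
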